### Randomisation

The randomisation sequence will be created prior to study commencement using
http://www.randomization.com. A 1:1 allocation in block sizes of 10 and stratified by gender will be used. Group allocation will be concealed from the blinded assessor using sequentially numbered sealed opaque envelopes, colour coded by gender. Envelopes will be opened with the participant by the treating physiotherapist, after baseline assessments have been completed. Gender stratification is necessary to avoid weighting of sexes to any particular group, which may skew physical fitness data.

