## Methods

### Study design

This is a prospective, single blinded, randomised controlled trial. There are two arms (i) exercise intervention using arm ergometers and (ii) control. It will not be possible to blind the treating physiotherapist or the patient to the exercise intervention; hence the single (assessor) blinded design. The protocol was approved by the Beaumont Hospital Medical Research ethics committee in November 2009. The trial was designed incorporating recommendations of the CONSORT statement
[24]. The flow of participants through the study is represented in Figure 
1. All participants will receive usual Physiotherapy care, which does not routinely include arm ergometry. Participants in the control group can choose to cross over to the exercise intervention arm after the eight week control period. Assessments will be completed at baseline and at eight weeks.

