### Setting

The study will be based in Beaumont Hospital, Dublin. Assessments will be conducted in the Physiotherapy department and the exercise intervention will be completed in the participants’ homes.

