### Participants

Patients will be recruited from medical and physiotherapy post Polio clinics and through advertisement in the national post polio support group publication. Eligibility criteria are shown in Table 
1. Information leaflets will be provided, as well as a detailed verbal explanation and questions answered. All potential participants will be screened for suitability by a medical doctor using the PAR-med-X screening tool. A letter will be sent to each recruited patients’ general practitioner, outlining the details of the study and requesting that they contact the researchers should they have any concerns about their patients’ participation. Prior to baseline assessment written informed consent will be obtained. Participants will be free to withdraw at any time.

**Table 1 T1:** Eligibility criteria

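### A single fixed block size of 10 within gender lets whoever tallies the opened envelopes predict up to 1 in 6 allocations with certainty; randomly varied block sizes would remove most of that at little cost

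*Protocol article*

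**What the plan says.** The Randomisation section of the protocol article fixes one block length for the whole trial: "A 1:1 allocation in block sizes of 10 and stratified by gender will be used". The allocations are held in "sequentially numbered sealed opaque envelopes, colour coded by gender", so each gender has its own running sequence. On who handles them it says: "Envelopes will be opened with the participant by the treating physiotherapist, after baseline assessments have been completed". The concealment statement names one person: "Group allocation will be concealed from the blinded assessor".

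The Study design section says of the person opening the envelopes: "It will not be possible to blind the treating physiotherapist or the patient to the exercise intervention". The Setting section gives one location: "The study will be based in Beaumont Hospital, Dublin". The Sample size section sets the target at 120 participants, 60 per group.

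**The concern.** Sealed opaque envelopes hide the next assignment from sight, but they do not stop it being inferred. With 1:1 allocation in blocks of 10, each block holds exactly five places per arm. Once five of one arm have been opened, the rest of the block is known. Making that inference takes the block length and a record of what has been opened in that gender. The treating physiotherapist sees each allocation when the envelope is opened, and a member of the trial team can be expected to know the block length. With one hospital, each gender has a single stream to follow.

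At stake is selection bias. If someone who can foresee the next arm also affects whether or when a particular patient enters, the two groups may differ in prognosis for reasons that randomisation was meant to exclude. The Statistical analysis section compares groups with two-sample t-tests or their non-parametric equivalent and mentions no covariate adjustment, so the comparison as described would not correct for such a difference.

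**Working it through.** The document gives no figure for predictability, so there is none to reproduce.

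**Inputs**
- Block size 10, ratio 1:1, two gender strata (Randomisation): m = 5 places per arm in each block.
- Total of 120 participants (Sample size).
- Assumption: the observer knows the block size and has a complete tally of earlier allocations by gender.

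**Step 1: allocations known with certainty in a complete block.** There are C(10,5) = 252 equally likely arrangements. An allocation is certain when one arm's five places are already used, which means it belongs to the final run of identical allocations.

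| Position in block | Probability that it is certain |
|---|---|
| 10th | 1 |
| 9th | 2 × C(8,5)/252 = 112/252 = 0.444 |
| 8th | 2 × C(7,5)/252 = 42/252 = 0.167 |
| 7th | 2 × C(6,5)/252 = 12/252 = 0.048 |
| 6th | 2 × C(5,5)/252 = 2/252 = 0.008 |

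The sum is 1.667 per block. The closed form agrees: 2m/(m + 1) = 10/6 = 1.667. As a share this is 1/(m + 1) = 1/6 = 16.7%. At least two allocations are certain in 44% of blocks.

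**Step 2: the whole trial.** If all 12 blocks are completed, 12 × 1.667 = 20 of 120. If the gender split leaves a part-filled last block in each stratum, some certain positions are never reached. The worst case over splits from 20:100 to 100:20 includes 25:95. There, 11 blocks are complete and each of the two open blocks stops at its fifth place, giving 11 × 1.667 = 18.3, or 15.3%. The range is therefore 18.3 to 20.

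**Step 3: better-than-chance guessing.** The observer always guesses the arm with more places left and tosses a coin when they are equal. The expected number of correct guesses per block is m + 2^(2m−1)/C(2m,m) − 1/2 = 5 + 512/252 − 0.5 = 6.53 of 10, or 65.3%, against 50% by chance.

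**Step 4: comparison with other fixed sizes.**

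| Fixed block size | Certain, 1/(m + 1) | Correct guesses |
|---|---|---|
| 4 | 33.3% | 70.8% |
| 6 | 25.0% | 68.3% |
| 8 | 20.0% | 66.6% |
| 10 | 16.7% | 65.3% |

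**Step 5: randomly varied block sizes.** Sequences of 60 were simulated with sizes drawn at random with equal chance. The observer knew the set of sizes but not their order, and tracked every allocation. The share of certain allocations was about 2.0% for sizes 4/6/8, 1.8% for 6/8/10 and 1.4% for 8/10/12. For 6/8/10 this is about 0.018 × 120 = 2 participants, against 18 to 20 now. The gain lies in certainty. The last column of the Step 4 table gives no reason to expect fewer correct guesses from mixing in shorter blocks, and a simulation of the same observer confirmed that the guessing rate stays at roughly its present level.

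**The case against.** The strongest reply is that no route from prediction to biased entry is documented. Nothing in the article says that the treating physiotherapist enrols, judges eligibility or books patients. The Participants section has a medical doctor screen every candidate. Several entry criteria in Table 1 are measured thresholds. Consent precedes baseline assessment, and the envelope is opened only after that assessment. A block of 10 is also less predictable than the smaller fixed blocks in the table above. All of this stands. It limits the point to a risk and keeps it minor. It does not remove the point, because prediction needs only the block size and the tally, and it works before the next patient is booked.

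Some stronger readings are tempting but are not supported:

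- **Detection bias through the assessor.** A reader might infer that predictable blocks weaken the assessor's blinding. After opening, the physiotherapist knows the actual arm under any block scheme. A leak before the eight-week assessment would pass on that knowledge and not a guess, so block size is not the cause. The same holds for self-reported outcomes, because participants are unblinded anyway.
- **Bias that the data could not reveal.** The Statistical analysis section says baseline comparability will be examined. Selection on measured features could show there.
- **Recruitment controlled by physiotherapy.** The Participants section says "Patients will be recruited from medical and physiotherapy post Polio clinics", and the sentence goes on to name advertisement in the support group's publication. It does not say that the treating physiotherapist staffs any of these clinics.
- **Envelope custody as a gap.** Who prepares and holds the envelopes is detail that a journal article may leave to the full protocol.
- **A block size that was public during recruitment.** The document does not show this. The point needs only that trial staff know the size.

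**Conclusion.** The point holds as a low-cost improvement. One fixed block size within gender, combined with an unblinded person opening the envelopes at a single hospital, allows up to 1 in 6 allocations to be predicted with certainty: 18.3 to 20 of 120. Overall, about 65% can be guessed correctly. These are upper figures, because they assume an observer who knows the size and keeps a complete tally by gender. They become selection bias only if that observer, or someone who shares the tally, affects who enters or in what order, and the document does not show this. The effect on the treatment estimate cannot be sized from the document. The weakness is that the size is fixed and knowable, not that it is too small.

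**What to change.** Generate the sequence, or its unused remainder if recruitment has begun, with randomly varying block sizes within each gender, for example 6, 8 and 10. Keep the sizes from staff who recruit, treat or assess. On the assumptions above this cuts certain allocations from 16.7% to about 2%, even for an observer who learns the set of sizes. It does not abolish better-than-chance guessing, which is why the sizes should also be withheld.

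The cost is one new run of the sequence generator and re-packing of unused envelopes. Sample size, visits, outcomes and analysis do not change. The downside is slightly less exact balance within gender if recruitment stops mid-block.

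If enrolment is already complete, the useful step is to report who enrolled and ordered participants and who knew the block size.

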### Intervention

Participants randomised to the intervention group will exercise at home using arm ergometers for eight weeks. The treating physiotherapist will provide an individualised exercise programme during a home visit. Participants will receive a static cycle, which placed on a table is used as an arm ergometer, a polar heart rate monitor and an exercise log/instruction booklet.

Participants will begin exercising for at least ten minutes per day three days per week. If an individual has difficulty exercising for 10 minutes continuously, the 10 minute session may be broken into two to three minute bursts of exercise, with one minute rests
[15,26]. Participants will aim to increase exercise durations to 30 minutes per day three to five days per week. Participants will be educated regarding the target of ACSM recommendations of a cumulative 150 minutes of moderate intensity exercise per week
[7].

Participants will exercise at a moderate intensity
[7,27]. Maximum heart rate (MaxHR=220-age) will be used to prescribe a target exercising heart rate of 50-70% HRMax in addition to a subjective level of 13–17 on the BORG rate of perceived exertion (RPE). This exercise prescription meets recommendations for exercise in Polio survivors and is similar to those previously conducted and tolerated in this group
[16,19]. Prescription using HRMax has been recommended for use in this group as difficulties have been reported in achieving target heart rate using Karvonen’s formula, due to high resting heart rates
[15].

Exercise intensity will be modified by changing pedal rate or resistance and monitored using the polar heart rate monitors. The treating physiotherapist will educate participants on how to alter exercise intensity based on exercising heart rate. Exercise time, heart rate and RPE will be recorded by the participant in the exercise log for each exercise session. Participants will pedal with zero resistance for 2 minutes prior to the exercise session, to warm up and will be provided with upper limb range of movement exercises and stretches as cool down exercises.

Participants will monitor fatigue and pain on 0–10 Visual Analogue Scales. If there is an increase of more than 2 points in upper limb, neck or back pain, or subjective fatigue, the participant will be advised to reduce exercise duration and/or intensity. If this does not result in an improvement, the participant will be advised to contact the treating physiotherapist by phone. This physiotherapist will then make a decision on how to proceed and the participant will be managed appropriately and withdrawn from the study if necessary. All adverse events will be recorded and managed according to a detailed policy. Participants randomised to the control group will be advised to continue with normal activities and will receive physiotherapy care as appropriate.

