**Discussion:**

The efficacy of a home-based arm ergometry programme in Polio survivors will be examined. No previous trial has examined such a programme using a wide range of outcome measures pertinent to Polio survivors. This study will provide new information on the impact of arm ergometry on physical fitness, activity, body composition, fatigue, pain, muscle strength, and health related quality of life. Also, the study will provide information, which at present is lacking, on safety of aerobic exercise in Polio, as potential negative outcomes of activity including loss of muscle strength, increased pain and fatigue will be closely monitored.

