[23]. An appropriate aerobic exercise programme may enable Polio survivors to improve physical fitness, enjoy the health benefits associated with exercise
[7] and perhaps reduce fatigue. A convenient and accessible form of exercise is likely to maximise compliance as Polio survivors are advised to exercise when subjective energy levels are good, to avoid exacerbating fatigue
[13,14]. A small ergometer, provided for use at home may be an affordable option meeting these requirements.

The aim of this randomised controlled trial is to investigate the effect of an aerobic exercise programme, carried out in the home environment, using arm ergometers, on Polio survivors. We hypothesise that upper limb aerobic training will result in a significant increase in fitness in exercising Polio survivors compared with Polio survivors allocated to a control group. Completing the exercise programme is also predicted to improve activity, energy cost of walking and health related quality of life without increases in pain and fatigue.

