### Statistical analysis

Data will be coded and collated in a Microsoft Excel® spreadsheet and Stata 12 will be used for statistical analysis. All analyses will be conducted on an intention-to-treat principle
[49]. Missing data will be managed using the last observation carried forward method. Per-protocol analyses will be performed excluding participants with major deviations from the treatment protocol (defined as less than 50% compliance with treatment). Demographic characteristics and baseline data will be summarised using descriptive statistics and baseline comparability of the groups will be examined. The distribution of the data will be assessed and if appropriate, parametric methods will be used in analysis. Two sample t-tests will be used to compare groups and paired t-tests will be used for within group comparisons. The non-parametric equivalent will be used where data are not normally distributed. A significance level of p<0.05 will be set. The primary analysis will examine the difference between intervention and control groups. A secondary analysis will compare pre and post intervention scores and will include control participants who crossed over to the intervention group.

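### The withdrawal rule for exercisers with unresolved pain or fatigue does not separate stopping exercise from leaving follow-up, so baseline carried forward can hide worsening in those two outcomes

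*Protocol article*

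**What the plan says.** The protocol article deals with this in four places.

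- **Methods, Intervention.** Exercisers rate pain and fatigue on 0–10 visual analogue scales. The trigger is "If there is an increase of more than 2 points in upper limb, neck or back pain, or subjective fatigue". The first step is to cut exercise duration or intensity. If that does not help, the participant phones the treating physiotherapist, who decides how to proceed: "the participant will be managed appropriately and withdrawn from the study if necessary". For the other arm the section says "Participants randomised to the control group will be advised to continue with normal activities", along with physiotherapy as appropriate. It states no symptom trigger or withdrawal step for controls. Adverse events are to be recorded in both arms under a policy that is not shown.
- **Methods, Study design.** "Assessments will be completed at baseline and at eight weeks". There is no visit in between.
- **Methods, Statistical analysis.** "All analyses will be conducted on an intention-to-treat principle", and "Missing data will be managed using the last observation carried forward method". A per-protocol analysis leaves out participants whose compliance is below 50%.
- **Background and Discussion.** The hypothesis predicts improvement in activity, walking cost and "health related quality of life without increases in pain and fatigue". The article presents safety as a contribution of the trial and says that "potential negative outcomes of activity including loss of muscle strength, increased pain and fatigue will be closely monitored".

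**The concern.** An intention-to-treat comparison needs the week-8 outcome of everyone randomised, however much they exercised. The Intervention section speaks of withdrawal from the study, and nowhere does the article say that a participant who stops exercising is still assessed at week 8. Taken at its word, the rule can end follow-up for a reason closely related to two of the trial's own outcomes, pain and fatigue. As written it can do so only in the exercise arm, since its first step is to reduce exercise.

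The missing-data rule adds to the problem. With two assessments, the last observation before withdrawal is the baseline value. A participant withdrawn because of worse pain or fatigue, and not seen at week 8, stays in the intention-to-treat set with a recorded change of zero. A participant who stops early may also fall below 50% compliance and so be left out of the per-protocol analysis. Both planned analyses could then miss the worsening that led to the withdrawal.

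At stake is the prediction of no increase in pain and fatigue, and the safety information the trial offers. An analysis plan written later cannot restore week-8 scores that were never collected.

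**Working it through.** **Inputs from the protocol article**
- 60 participants per group, 15% drop-out, and a clinically significant difference of 1 point on the Fatigue Severity Scale (FSS) (Sample size and its table).
- Trigger: a rise of more than 2 points on a 0–10 VAS (Intervention).
- Assessments at baseline and week 8 (Study design); last observation carried forward (Statistical analysis).

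**Inputs that are assumptions**
- Share of exercisers withdrawn under the rule and not seen at week 8: 5–15%, which is 0.05 × 60 = 3 to 0.15 × 60 = 9 people. The upper end equals the whole planned all-cause drop-out.
- Their true rise at week 8: 1–2 points on the FSS or, on the scale of the trigger itself, 2–4 VAS points. The article does not link the two scales.

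**Plan's own figure.** The group size used above can be reproduced: 2 × (14.5² / 8²) × 7.9 = 51.9, so 52 per group. Then 52 × 1.15 = 59.8, so 60 (dividing by 0.85 gives 61.2, so 62). The point does not depend on this figure. The article gives no rate of withdrawal for pain or fatigue, so there is no stated figure to check on that.

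**Step 1: what carrying forward does.** Let p be the share withdrawn, L their true mean change at week 8, and m the mean change of the other exercisers.
- True arm mean change = (1 − p) × m + p × L
- Arm mean change as analysed = (1 − p) × m + p × 0
- Hidden worsening = p × L

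**Step 2: numbers for pain and fatigue**

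| Share withdrawn | People of 60 | FSS rise of 1 | FSS rise of 2 | VAS rise of 2 | VAS rise of 4 |
|---|---|---|---|---|---|
| 5% | 3 | 0.05 | 0.10 | 0.10 | 0.20 |
| 10% | 6 | 0.10 | 0.20 | 0.20 | 0.40 |
| 15% | 9 | 0.15 | 0.30 | 0.30 | 0.60 |

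Each entry is p × L in points of the arm mean. If these participants attended week 8, the hidden amount would be 0.

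**Step 3: the primary outcome.** The trigger is not the Six-Minute Arm Test, so L could have either sign. Take a fall in heart rate as improvement.
- If those withdrawn would have shown a fall of 8 beats per minute, the analysed arm mean is too high by 0.05 × 8 = 0.4 to 0.15 × 8 = 1.2 beats, which works against exercise.
- If they would have shown a rise of 8 beats, it is too low by the same 0.4 to 1.2 beats, which favours exercise.
- If they would have shown no change, there is no bias.

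The documents do not say which case applies.

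**The case against.** The strongest reply is that loss of the week-8 outcome is inferred rather than stated. Withdrawal is a discretionary last step, after reduced exercise, a phone call and a decision by the physiotherapist. The article does not say that a withdrawn participant goes unassessed. The Statistical analysis section claims intention to treat and has a separate per-protocol analysis defined by compliance, which presupposes that people who largely stop exercising can stay in the trial. The wording may be a loose way of saying that exercise stops, and the full protocol or the adverse event policy, neither of which is shown, may settle follow-up. Adverse events are recorded in any case, so the episodes need not disappear from safety reporting.

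Part of this stands. How often the rule would lead to a lost assessment is unknown, and the sentence may mean less than it says. But the current text says withdrawal from the study, and nothing in the article keeps such participants for week 8. An adverse event record shows that something happened; it does not supply a week-8 pain or fatigue score.

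A reader might also infer more than the documents support:

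- **That the efficacy result is biased in favour of exercise.** Step 3 of the working shows that the bias in the primary outcome can go either way, and a zero change may dilute a real benefit.
- **That falling strength also removes people from follow-up.** The trigger names only pain and subjective fatigue. Strength is measured at the two clinic assessments and triggers nothing.
- **That the proportion worsening by more than 2 VAS points is understated by the full 5–15 percentage points.** The protocol defines no such endpoint, and the inference would need every case still to exceed 2 points at week 8.

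**Conclusion.** The concern holds for pain and fatigue. As written, a rule with no control-arm counterpart allows withdrawal from the study after unresolved symptoms, and two-visit follow-up with last observation carried forward turns any week-8 value lost in this way into no change. The effect is to understate worsening in the exercise arm on outcomes that the hypothesis and the safety aim are about.

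The size is unknown. Under the assumed shares and FSS rises it is 0.05–0.30 points, at most about a third of the 1-point difference the plan treats as clinically significant. It rests on three conditions: those withdrawn are not assessed at week 8, their rise is still present then, and baseline is carried forward. It is therefore partly a consequence of the missing-data rule and not of the withdrawal sentence alone.

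The text does not show that the intention-to-treat analysis as a whole fails, that the primary comparison favours exercise, or that the strength results are affected. The change is still worth making before the trial proceeds, because outcomes not collected cannot be recovered later.

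**What to change.** Reword the sentence in the Intervention section, and any matching text given to participants, so that:

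1. stopping or modifying exercise, at the treating physiotherapist's discretion and with the present decision rule unchanged, is distinct from leaving the study;
2. every randomised participant is invited to the planned week-8 assessment, or at least asked to complete the questionnaires, unless they withdraw consent for follow-up, which is recorded separately;
3. participants who stopped exercising are analysed in the group to which they were randomised;
4. the number of exercisers who stopped because of pain or fatigue is reported.

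This makes no proposal on when exercise should stop. The cost is a short change of wording and some effort to retain people who have stopped exercising. The week-8 assessment is already part of the design.
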